**SLIDE A - KK1.0 (30 + - 10 min)****(All Parasites Egg N°)**

| Factor |        |        |
|--------|--------|--------|
| 8      | 1
2 | 2
4 |

| Stool
TYP
E        |
|--------------------------|
|  |

1= Normal, formed  
(24)

2 = Pasty (12)

3= NON-LIQUID  
Diarrhea (8)Star  
t

|                          |                          |   |                          |                          |
|--------------------------|--------------------------|---|--------------------------|--------------------------|
|  |  | : |  |  |
| H                        | H                        |   | m                        | m                        |

End

|                          |                          |   |                          |                          |
|--------------------------|--------------------------|---|--------------------------|--------------------------|
|  |  | : |  |  |
| H                        | H                        |   | m                        | m                        |

Nega  
tive

|     |
|-----|
| Yes |
|-----|

Cont  
rol

|             |        |
|-------------|--------|
| Y
e
s | N
o |
|-------------|--------|

|                          |                          |                          |                          |                          |                          |                          |                          |                          |                          |                          |                          |                          |                          |                          |                          |
|--------------------------|--------------------------|--------------------------|--------------------------|--------------------------|--------------------------|--------------------------|--------------------------|--------------------------|--------------------------|--------------------------|--------------------------|--------------------------|--------------------------|--------------------------|--------------------------|
| 1                        | Ascaris                  | 2                        | Trichuris                | 3                        | Hookworm                 | 4                        | E.
vermicula
ris   | 5                        | H. nana                  | 6                        | H.
diminuta           | 7                        | Taenia                   | 8                        | Fasciola                 |
|  |  |  |  |  |  |  |  |  |  |  |  |  |  |  |  |
| 9                        | S.
stercoralis        | 10                       | Giardia                  | 11                       | Capilaria sp             | 12                       | D.
pacificum          | 13                       | Trichostron
gylus     | 14                       |                          | 15                       |                          | 16                       |                          |
|  |  |  |  |  |  |  |  |  |  |  |  |  |  |  |  |

**Day 2****SLIDE B - KK1.0 (24 H + - 4 H)****(All Parasites Egg N°)**

| Factor |        |        |
|--------|--------|--------|
| 8      | 1
2 | 2
4 |

| Stool
TYP
E |
|-------------------|
|                   |

1= Normal, formed  
(24)

2 = Pasty (12 )

3= NON-LIQUID  
Diarrhea (8)

| Star
t                |                          | End                      |                          |
|--------------------------|--------------------------|--------------------------|--------------------------|
|  |  |  |  |
| H                        | H                        | m                        | m                        |

| Nega
tive |
|--------------|
| Yes          |

| Cont
rol |        |
|-------------|--------|
| Y
e
s | N
o |

|                          |                          |                          |                          |                          |                          |                          |                          |                          |                          |                          |                          |                          |                          |                          |                          |
|--------------------------|--------------------------|--------------------------|--------------------------|--------------------------|--------------------------|--------------------------|--------------------------|--------------------------|--------------------------|--------------------------|--------------------------|--------------------------|--------------------------|--------------------------|--------------------------|
| 1                        | Ascaris           | 2                        | Trichuris         | 3                        | Hookworm          | 4                        | E. vermicularis   | 5                        | H. nana           | 6                        | H. diminuta       | 7                        | Taenia            | 8                        | Fasciola          |
|  |  |  |  |  |  |  |  |  |  |  |  |  |  |  |  |
| 9                        | S. stercoralis    | 10                       | Giardia           | 11                       | Capilaria sp      | 12                       | D. pacificum      | 13                       | Trichostrongylus  | 14                       |  | 15                       |  | 16                       |  |
|  |  |  |  |  |  |  |  |  |  |  |  |  |  |  |  |

**SLIDE B - KK2.0 (24 H + - 4 H)**

|                          |                          |   |                          |                          |
|--------------------------|--------------------------|---|--------------------------|--------------------------|
|  |  | : |  |  |
| H                        | H                        |   | m                        | m                        |

**QC (10 % at Random)****Day 1**

**Sedimentation (00 Hrs) [+ (2-5)/ ++ (6-10) / +++ (> 10)] (MARK only: 1, 2 or 3)**

\* Hookworm= Ancylostoma/Necator

[figure not shown]

Negative  
Yes

|   |                            |   |                            |   |                            |   |                            |   |                            |   |                            |          |                            |   |                            |   |                            |    |                            |
|---|----------------------------|---|----------------------------|---|----------------------------|---|----------------------------|---|----------------------------|---|----------------------------|----------|----------------------------|---|----------------------------|---|----------------------------|----|----------------------------|
| 1 | Ascari
s                | 2 | Trichuris                  | 3 | Hookwor
m *             | 4 | E.
vermicu
laris     | 5 | H.
nana                 | 6 | H.
diminut
a         | 7        | Taenia                     | 8 | Fasciol
a               | 9 | S.
stercoral
is      | 10 | Giardia                    |
|   |  + |   |  + |   |  + |   |  + |   |  + |   |  + |          |  + |   |  + |   |  + |    |  + |
| 1 | Capilla
ria sp          | 1 | D.
pacificum            | 1 | Trichostro
ngylus       | 1 |                            | 1 |                            | 1 |                            | Comments |                            |   |                            |   |                            |    |                            |
|   |  + |   |  + |   |  + |   |  + |   |  + |   |  + |          |                            |   |                            |   |                            |    |                            |

**SLIDE A - KK1.0 (30 + - 10 min)  
(All Parasites Egg N°)**

| Factor |   |   |
|--------|---|---|
| 8      | 1 | 2 |
|        | 2 | 4 |

| Stool
TYP
E |
|-------------------|
|                   |

1= Normal, formed  
(24)  
2 = Pasty (12)  
3= NO N- LIQUID  
Diarrhea(8)

[figure not shown]

Negative  
Yes

|   |                          |   |                          |   |                          |   |                          |   |                          |   |                          |   |                          |   |                          |
|---|--------------------------|---|--------------------------|---|--------------------------|---|--------------------------|---|--------------------------|---|--------------------------|---|--------------------------|---|--------------------------|
| 1 | Ascaris                  | 2 | Trichuris                | 3 | Hookworm                 | 4 | E.
vermicula
ris   | 5 | H. nana                  | 6 | H.
diminuta           | 7 | Taenia                   | 8 | Fasciola                 |
|   |  |   |  |   |  |   |  |   |  |   |  |   |  |   |  |

|   |                                                                         |        |                                                                         |        |                                                                         |        |                                                                         |        |                                                                         |        |                                                                         |        |                                                                         |        |                                                                         |
|---|-------------------------------------------------------------------------|--------|-------------------------------------------------------------------------|--------|-------------------------------------------------------------------------|--------|-------------------------------------------------------------------------|--------|-------------------------------------------------------------------------|--------|-------------------------------------------------------------------------|--------|-------------------------------------------------------------------------|--------|-------------------------------------------------------------------------|
| 9 | S.
stercoralis                                                       | 1
0 | Giardia                                                                 | 1
1 | Capilaria sp                                                            | 1
2 | D.
pacificum                                                         | 1
3 | Trichostron
gylus                                                    | 1
4 |                                                                         | 1
5 |                                                                         | 1
6 |                                                                         |
|   | 

 |        | 

 |        | 

 |        | 

 |        | 

 |        | 

 |        | 

 |        | 

 |

  

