## **Measures of Effectiveness/Clinical Response**

At the laboratory, trained laboratory technicians will prepare stool-thick-smear slides for KK1.0, KK2.0, and stool concentrations for the TSET method and will be read manually and by the KK2.0 method at specific timepoints and in accordance with standard process for each test. Slide images read by the AI-DP tool will be uploaded to the EggInspector application in the cloud database, then manually verified by an expert parasitologist in Peru. Validated results will be uploaded to the study database.

Definitions of appropriate measures of effectiveness/clinical response are as follows:

- KK1.0 method: The microscopy diagnostic standard for diagnosing STH infection intensity. Stool samples are made into a slide smear in which eggs are counted.
- KK2.0 method: An improved diagnostic technique over KK1.0 in development that uses AI-DP technology to facilitate egg counting without using a microscope. Using the KK thick smear technique, stool slide smear will be inserted into a slide scanner to provide an automated egg count. At present, this is a hybrid methodology that uses AI-DP and an expert parasitologist verification.
- TSET method: A qualitative method commonly used in LATAM to monitor for STH infection using a concentration by sedimentation assay, without centrifugation.
- Positive to any STH species: If any egg of that STH species is identified by any of the methods.

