#### 3.4.2. Measures of Effectiveness/Clinical Response

##### 3.4.2.1. Effectiveness/Clinical Response Measures

At the laboratory, trained laboratory technicians will prepare stool-thick-smear slides for KK1.0, KK2.0, and stool concentrations for the TSET method and will be read manually and by the KK2.0 method at specific timepoints and in accordance with standard process for each test. Slide images read by the AI-DP tool will be uploaded to the EggInspector application in the cloud database (see EggInspector Quick Start Guide), then manually verified by an expert parasitologist in Peru. Validated results will be uploaded to the study database.

Definitions of appropriate measures of effectiveness/clinical response are as follows:

- KK1.0 method: The microscopy diagnostic standard for diagnosing STH infection intensity. Stool samples are made into a slide smear in which eggs are counted.
- KK2.0 method: An improved diagnostic technique over KK1.0 in development that uses AI-DP technology to facilitate egg counting without using a microscope. Using the KK thick

smear technique, stool slide smear will be inserted into a slide scanner to provide an automated egg count. At present, this is a hybrid methodology that uses AI-DP and an expert parasitologist verification.

- TSET method: A qualitative method commonly used in LATAM to monitor for STH infection using a concentration by sedimentation assay, without centrifugation.
- Positive to any STH result: Any sample with egg(s) of any STH species identified by any of the diagnostic methods.

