### 4.3. Data Analyses

#### 4.3.1. Data Analyses

Descriptive summaries will be provided by diagnostic method and STH species. All continuous variables will be summarized using descriptive statistics, which will include the number of children, mean, standard deviation, median, minimum, and maximum. A 95% confidence interval (CI) will also be provided for EPG and sensitivity. All categorical variables will be summarized using frequencies and percentages. Summary and analysis will be provided by diagnostic method, STH species, and timepoints (30 minutes and 24 hours). It should be noted that at the 24±4-hour timepoint the same slide (Slide B), will be evaluated by both the KK1.0 and KK2.0 methods. While at the 30-minute timepoint, different slides (slides A and B) from the same stool sample will be evaluated by the same 2 methods. Therefore, extra caution should be exercised when comparing results from the different methods at the 30-minute timepoint since 2 different slides are being analyzed.

Egg load will be classified into 3 intensity categories as detailed below according to EPG:

- *A. lumbricoides*: Low: <5,000 EPG; Moderate: 5,000-49,999 EPG; Heavy: >50,000 EPG
- *T. trichiura*: Low: <1,000 EPG; Moderate: 1,000-9,999 EPG; Heavy: >10,000 EPG
- Hookworms: Low: <2,000 EPG; Moderate: 2,000-3,999 EPG; Heavy: >4,000 EPG

Since TSET method cannot produce EPG, intensity of each STH species will only be derived for KK1.0 and KK2.0 methods.

Since no “gold” standard for egg counts exist in this study, a diagnostic pseudo “gold” standard will be created. A sample is considered to be truly positive if any diagnostic method comes back with a positive reading at any time of the study.

Number of total positive samples for a STH species is defined as

$$N(+) = N(KK1.0(+))_{30m} \cup KK2.0(+))_{30m} \cup KK1.0(+))_{24h} \cup KK2.0(+))_{24h} \cup TSET(+))$$

Where  $KK1.0(+))_{30m}$  indicates a positive sample based on KK1.0 at 30 minutes,  $KK2.0(+))_{30m}$  indicates a positive sample based on KK2.0 at 30 minutes,  $KK1.0(+))_{24h}$  indicates a positive sample based on KK1.0 at 24 hours,  $KK2.0(+))_{24h}$  indicates a positive sample based on KK2.0 at 24 hours, and  $TSET(+))$  indicates a positive sample based on TSET which is performed only once during the study.

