### **Analysis of Secondary Endpoints**

Prevalence of STH infection is defined as the percentage of children with positive egg count readings. Summary of prevalence will be provided by diagnostics method and STH species. If a child is diagnosed as positive for a STH species during anytime of the study, this child is considered STH infected.

Summary of the qualitative readings (1+, 2+, 3+) from TSET will also be provided.

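### The sedimentation (TSET) legend starts its lowest grade at a count of 2, so a count of one has no positive code although the protocol calls any egg positive; TSET positives, and under a further condition N(+), may be undercounted

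*Protocol*

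**What the plan says.** **Definition of positive.** The synopsis (Measures of Effectiveness/Clinical Response) states: "Positive to any STH species: If any egg of that STH species is identified by any of the methods". Section 3.4.2.1 gives the same rule at sample level: "Any sample with egg(s) of any STH species identified by any of the diagnostic methods". Neither exempts TSET or sets a minimum above one egg.

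**Form.** In Attachment 1, under "QC (10 % at Random", the Day 1 sedimentation legend reads "2-5)/ ++ (6-10) / +++ (> 10)] (MARK only: 1, 2 or 3", with the range 2-5 attached to a single plus. A separate box marks a negative result. The manual Kato-Katz blocks on the same form ask for the number of eggs.

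**Analysis.** Section 4.3.1 builds the reference standard as a union of five readings: "A sample is considered to be truly positive if any diagnostic method comes back with a positive reading at any time of the study". The TSET term "indicates a positive sample based on TSET which is performed only once during the study". The resulting N(+) is the denominator of every sensitivity. Under Analysis of Secondary Endpoints: "Summary of the qualitative readings (1+, 2+, 3+) from TSET will also be provided". No lower positive level is mentioned.

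**Procedure.** Section 3.1.1 has the TSET technician count the eggs, although it describes the resulting data as qualitative.

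**The concern.** Taken literally, the printed scale sets a stricter positivity threshold for TSET (two or more) than for manual Kato-Katz (one or more, because the number is written down). The protocol's own definition makes no such distinction. The technician who sees one egg has no instruction: the sample can be marked 1, left ungraded, ticked negative or described under comments. Whether it counts as TSET(+) then depends on the individual reader.

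Two quantities are exposed: TSET prevalence, which belongs to the secondary endpoint, and N(+), the denominator of the primary sensitivity estimates. Any loss falls on light infections, where Section 1.3 says Kato-Katz is least sensitive and a TSET-only positive does most to complete the reference standard. The legible TSET block stores only a grade, so a one-egg sample marked negative cannot be identified later from that block.

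**Working it through.** The plan states no figure that depends on this point, so there is none to reproduce. The sample size of 500 is pragmatic.

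**1. Counts mapped through the legend.**

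| Count | Form | Any-egg definition |
|---|---|---|
| 0 | negative box | negative |
| 1 | no grade | positive |
| 2-5 | + | positive |
| 6-10 | ++ | positive |
| over 10 | +++ | positive |

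The only gap among counts of at least one is exactly one.

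**2. Effect on TSET(+).** Let g be the share of samples with at least one TSET egg that have exactly one. If none of them is graded, TSET prevalence is multiplied by (1-g). The documents give no egg-count distribution. Under assumed negative-binomial counts, g = P(X=1)/(1-P(X=0)):

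| Mean count | k = 0.1 | k = 0.3 | k = 1.0 |
|---|---|---|---|
| 1 | 33.5% | 41.8% | 50.0% |
| 5 | 20.4% | 20.7% | 16.7% |
| 20 | 14.2% | 11.6% | 4.8% |
| 100 | 10.0% | 6.3% | 1.0% |

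The range, about 1% to 50%, shows how strongly g depends on the assumption.

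**3. Effect on N(+).** N(+) is a union of KK1.0 and KK2.0 at 30 minutes, KK1.0 and KK2.0 at 24 hours, and TSET. A one-egg TSET sample leaves it only if all four Kato-Katz readings are negative. With f the share of the true union lost this way, the denominator shown is (1-f) times the true one. The Kato-Katz numerators are unchanged, because those samples are Kato-Katz negative. Hence

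sensitivity shown = true sensitivity / (1-f).

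| f (assumed) | true 60% | true 80% |
|---|---|---|
| 0 | 60.0% | 80.0% |
| 2% | 0.60/0.98 = 61.2% | 0.80/0.98 = 81.6% |
| 5% | 0.60/0.95 = 63.2% | 0.80/0.95 = 84.2% |
| 10% | 0.60/0.90 = 66.7% | 0.80/0.90 = 88.9% |

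**4. A plausible range for f.** An assumed joint model used gamma-distributed egg density (mean 50 to 1,000 EPG, k 0.1 to 0.3), Poisson counts, two smears of 1/24 g, TSET examining 1/24 g to 1 g, perfect reading, and every one-egg TSET sample left ungraded. It gave f between 2% and 11%, and a rise of about 2 to 8 points in one smear's apparent sensitivity. None of these inputs is in the documents. If Kato-Katz catches every such sample, or technicians mark one egg as 1, f is zero.

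**5. Effect on the KK2.0 to KK1.0 comparison.** Both sensitivities share the same N(+), so the factor 1/(1-f) cancels in their ratio. Their difference is scaled by it: at f = 5%, 80% minus 60% = 20 points becomes 20/0.95 = 21.1 points. The permutation in Section 4.3.1 swaps readings within a child. A child negative on all four Kato-Katz readings contributes nothing to either numerator under any swap, and N(+) stays fixed. Observed and permuted differences are scaled alike, so the p-value is the same with or without those children.

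**The case against.** - **The legend comes from the quality-control block.** This stands. The Day 1 heading is not legible, and only plus boxes of the same kind survive. A shared scale is a fair inference, not a shown fact. If Day 1 used another scale, the recounts would be graded differently from the readings they check, which would also need correcting.
- **The form does not tell staff to call one egg negative.** This stands. A technician who follows the any-egg definition could mark 1, and nothing would be lost. A reader might infer that one-egg samples cannot be recorded as positive and so are undercounted; the documents support only that they may be.
- **The unit is not stated.** This stands. The legend does not say per preparation or per field, and the same scale covers *Giardia*. The separate laboratory protocol or the data-capture manual, neither at hand, may settle it. Reading the legend as total eggs is an assumption.
- **The comparison of KK2.0 with KK1.0 is untouched.** This stands for the sensitivity ratio and the permutation test. Kato-Katz EPG, agreement and intensity do not use TSET. A reader might infer that the form favours one Kato-Katz method; it does not.
- **The study is descriptive.** True, but that does not remove the point. Absolute sensitivities with confidence intervals are planned outputs, and a denominator that depends on reader discretion affects them whether or not a hypothesis is tested.

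**Conclusion.** The mismatch is in the text: the legible TSET scale has no positive code for a count of one, and the protocol defines any egg as positive. The consequence is conditional. TSET positives and TSET prevalence are undercounted only if one-egg samples are left ungraded or marked negative. N(+) is undercounted only if, in addition, all four Kato-Katz readings are negative. Absolute Kato-Katz sensitivities are then too high by the factor 1/(1-f). The sizes shown rest on assumed values of f and assumed egg distributions, and zero remains possible.

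It would be wrong to carry the TSET shares in step 2 of the working over to N(+). They are shares of TSET positives, and the loss from the union cannot exceed the number of TSET positives lost. The point merits correction before samples are read, because the loss may be irrecoverable and the remedy is nearly free. It does not undermine the comparison of KK2.0 with KK1.0.

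**What to change.** Reconcile the form with the any-egg definition for the study analysis:

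- In both the Day 1 and quality-control sedimentation blocks, and in the eCRF, add an explicit code for a count of one, or record the egg count beside the grade.
- State the counting unit in the legend.
- In Section 4.3.1, define TSET(+) as any egg of the species seen, in line with the synopsis and Section 3.4.2.1.

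This concerns only how the reading is coded and analysed in the study. How TSET results are reported to families stays with the local standard of care.

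The cost is one form line and one eCRF field. No extra reading is needed, because the technician already counts the eggs.
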